**Fig. 2 Fig2:**
[figure not shown]
Schedule of enrolment, interventions, and assessments

Patients will undergo a review of hematological parameters including routine blood, biochemistry, electrolyte, and blood gas analysis on POD 4. Clinical pulmonary infection score (CPIS) [27] (Additional file 2) will be calculated on POD 4. The incidence of various postoperative complications, mortality rate, and LOS during hospitalization will be also recorded. At the same time, the incidence of postoperative complications especially PPCs, readmission, and mortality rates will be calculated within 30 and 90 PODs, respectively. This protocol has been approved by the Independent Ethics Committee (IEC) for Clinical Research of Zhongda Hospital, Affiliated to Southeast University (2021ZDSYLL203-P01), and is registered on the Chinese Clinical Trial Registry (ChiCTR2100049311). Only the head of this series of research (YR) has the right to make the final decision to terminate the trial if any serious adverse event judged to be related to the study treatment occurs.

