### Intervention

After signing informed consent, participants will be enrolled and randomly assigned to either the APP group or the control group. Surgical treatment will be performed on an emergency basis upon completion of the necessary pre-operative preparations. The surgical procedures, including closed reduction and internal fixation, THA, and HHA, will be decided by the chief physician (HC and YR) in trauma orthopedics. All operations will be scheduled in a fixed operating theatre and completed by the same team. Patients in the APP group will receive the prone position for at least half an hour at a time, and at least once per day for the first three consecutive PODs. The first APP treatment each day will be guided and supervised. The frequency and duration of other spontaneous prone positions of patients in the APP group will not be constrained. Except for this, during this period, all patients will receive the same postoperative management including postoperative oxygen inhalation (2L/min) for 6 h, standardized nutritional support, anti-inflammatory, detumescent, analgesic, hypodermic anti-coagulant prophylaxis, and regular atomization therapy. Both FNF and intertrochanteric fracture patients will roll onto their broken side into a prone position. Prone position pads will be used to suspend the upper abdomen and chest to reduce intra-abdominal and intra-thoracic pressure, allowing the alveoli to expand sufficiently. If severe adverse events such as unbearable pain, suspected prosthesis dislocation or internal fixation failure, chest tightness, and difficulty breathing occur, or the patients report that he/she cannot tolerate the prone position, the intervention should be stopped immediately. The investigators’ department will treat and compensate the patient for any additional injuries resulting from APP treatment. Intervention time as an adherence quantitative indicator and the reasons for intervention termination will be recorded in the database. Hematological parameters and chest radiography will be re-examined on the morning of POD 4. Patients will be followed up for at least 90 PODs through outpatient visits or telephone calls. In addition to orthopedic-related tests, they will undergo chest CT in an outpatient setting to determine if PPCs are present. The conduct of the trial will be audited weekly, independently of the investigators.

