### Secondary outcome

The secondary outcomes will be PaO_2_ on POD 4, the difference in PaO_2_ between POD 4 and EV, CPIS on POD 4, LOS, other types of postoperative complications, readmission, and mortality in 90-POD follow-up.

Given that FiO_2_ is equal to 20.9% of the breathing room air, we will use PaO_2_ instead of P/F to reflect the patient’s oxygenation capacity. On the morning of POD 4, the patient will undergo arterial blood gas analysis while inhaling room air. We anticipate that postoperative oxygenation (expressed as PaO_2_), will be higher in the APP group than in the control group. To minimize the impact of the baseline oxygenation capacity of different participants on the results, we will use the difference in PaO_2_ between POD 4 and EV to balance out this individual difference. Additional tests required for the diagnosis of complications, such as chest CT, pulmonary and coronary CT angiography, brain CT, arterial blood gas analysis, myocardial X-ray, troponin, and BNP, will be performed as soon as suspicious symptoms such as dyspnea, chest distress, fever, cough, sputum, and motor, sensory or cognitive dysfunction appear. All post-operative complications will be diagnosed following consultation with the appropriate specialist. Readmission and mortality rates within 30 or 90 PODs will be calculated separately. All serious adverse events, as well as all non-serious adverse events that are unexpected and determined to be related to the APP treatment, will be recorded in the study database and reported on request to the IEC for Clinical Research of Zhongda Hospital, Affiliated to Southeast University.

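### Serious adverse events are to be reported to the ethics committee on request, and the final decision to terminate rests with the research head alone, so no one independent of the team is assured of seeing serious harm as it accrues

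*Protocol article*

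**What the plan says.** Four places in the protocol article bear on this point.

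- **Secondary outcome (last sentence).** The events covered are "All serious adverse events, as well as all non-serious adverse events that are unexpected and determined to be related to the APP treatment". These "will be recorded in the study database and reported on request to the IEC". The article gives no other route by which events reach the committee.
- **Overview of trial design (paragraph after Fig. 2).** The head of the research, and nobody else, "has the right to make the final decision to terminate the trial if any serious adverse event judged to be related to the study treatment" arises. Who judges relatedness is not stated.
- **Intervention.** The initials given for the research head appear again here, as one of two chief physicians who decide which surgical procedure is used. The section ends: "The conduct of the trial will be audited weekly, independently of the investigators". In a patient who has a severe adverse event or cannot tolerate the position, "the intervention should be stopped immediately".
- **Blinding.** Participants and care providers are not blinded. Outcome assessors and data analysts are.

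**The concern.** A committee that receives events when it asks for them has to know that there is something to ask about. If the rule is followed literally, a serious event is written into the trial's own database and need go no further until a request arrives.

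The decision to terminate is reserved to one person, who leads the research and also has a clinical role in an unblinded trial. The stated trigger is a single serious event judged related to the intervention. Deaths and pulmonary emboli also occur after hip fracture surgery without APP, so individual cases can reasonably be judged unrelated. An excess of such events would show only in a comparison of counts between arms, and the text assigns that comparison to nobody independent while the trial is running.

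What is at stake is patient safety and the credibility of the harm data. The patients are over 65, must have at least one listed risk condition to be eligible, and receive an intervention for which the Discussion knows of no report in the orthopedic field. The Intervention section itself anticipates suspected dislocation, fixation failure and breathing difficulty. No estimate or test in the analysis plan depends on this point.

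**Working it through.** The point is procedural and the plan gives no figure to reproduce. The check is a side-by-side reading, plus one calculation on whether the pilot makes the reporting route immaterial.

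**1. Who is assured of seeing serious events as they accrue?**

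| Party | What the article says | Independent of the team? | Assured of seeing serious events? |
|---|---|---|---|
| Ethics committee | Receives events on request (Secondary outcome) | Yes | No: depends on a request |
| Weekly audit | Covers conduct of the trial (Intervention) | Yes | Not stated: no remit on adverse events, recipient or stopping power is given |
| Research head | Sole holder of the final decision to terminate (Overview) | No: also a chief physician choosing procedures | Implied by the role |
| Holder of the final dataset | One investigator, who shares it with team members on request (Data collection and analysis plan) | No | Concerns the final dataset, not accruing events |

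No row is both independent and assured. That follows from rules the article states, not from its silence about a monitoring committee.

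**2. Does the pilot make the route immaterial?**

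Input: no dislocation or fixation failure in 42 APP patients in the preliminary trials (Discussion, Prone position in geriatric patients with hip fracture).

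Formula: with 0 events in n patients, the exact upper bound for the true risk is 1 − α^(1/n).

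- One-sided 95% bound: 1 − 0.05^(1/42) = 0.0688, or 6.9%.
- Upper limit of the two-sided 95% interval: 1 − 0.025^(1/42) = 0.0841, or 8.4%.

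Applied to the planned 100 APP patients: 100 × 0.0688 = 6.9 and 100 × 0.0841 = 8.4, so about 7 to 8 affected patients would still be compatible with the pilot. The calculation concerns these two complications only. It shows that the pilot cannot stand in for a reporting route; it does not measure how many events the on-request rule would leave unreported.

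**3. What reporting load would a fix create?**

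Recruitment of 200 patients from September 2021 to December 2024 spans 40 months: 200 / 40 = 5 patients a month on average. Prompt individual reports plus a periodic table is a light task at that pace. A by-arm table every week would be more than the pace calls for.

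**The case against.** The strongest reply has four parts.

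- **Wording.** The sentence does not say that events go to the committee on request and in no other way, and in loosely phrased English it may mean as the committee requires. That is possible, but the printed rule still does not commit the team to unsolicited reporting, and no standing requirement is cited. If the milder meaning is intended, the fix simply says so.
- **Condensed article.** Reporting timelines, causality procedures and monitoring arrangements commonly sit in the full protocol. This is right, and neither the absence of a monitoring committee nor of timelines is counted here. The point rests on two affirmative rules: reporting on request, and termination decided by the head alone.
- **Existing protections.** The first prone session each day is supervised, the intervention stops at once in a patient with a severe event, reasons for stopping are recorded, and complications are diagnosed with specialist consultation. These are real, but they protect the individual patient and give nobody outside the team the accumulating picture.
- **The audit.** Serious events must be recorded in the database, and an audit of conduct could look there. This stands as a possibility: a reader might infer that the audit excludes safety, but the article states no such limit. Equally, it gives no assurance that safety is covered.

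A reader might also infer that the research head operates on the patients, that the intervention is wholly untested, or that every adverse event falls under the on-request rule. The text supports none of these. Chief physicians decide the procedure and the same team completes the operations; 42 pilot patients were assigned to APP; and the rule covers serious events and unexpected related non-serious ones.

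**Conclusion.** The point holds as a badly fixed rule. Read as written, the article does not assure that anyone independent of the team sees serious adverse events as they accrue, and it places the final decision to terminate with one investigator who also has a clinical role. The pilot leaves room for a true risk of dislocation or fixation failure of about 7% (one-sided 95% bound; 8.4% as the two-sided upper limit), so the gap cannot be dismissed on prior safety data.

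This rests on three assumptions: that the on-request wording is meant literally, that no unshown document overrides it, and that the matching initials denote one person.

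Two stronger conclusions should not be drawn. One is that harm would certainly go unseen: the committee may ask, and the audit may look. The other is that the ethics committee has lost its power over the trial: the article reserves the final decision to the research head but does not say that this displaces the body that approved the study. Nor does the article say that the head judges relatedness, or that a related serious event is the only ground for ending the trial. The size of the rule's effect on reporting cannot be calculated from the document.

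**What to change.** 1. **Secondary outcome.** Replace reporting on request with prompt, unsolicited reporting to the ethics committee of every serious adverse event in either arm, whatever its judged relation to APP. Add periodic cumulative counts by coded arm; the A/B labels already planned for the analysts would serve.
2. **Overview of trial design.** Reconcile the termination sentence with the committee's oversight by stating that the research head's decision does not limit the committee's authority.
3. **Intervention.** Say in one clause whether the weekly audit reviews adverse events.

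The cost is an amendment to the wording and a small additional reporting task, at about five patients recruited a month on average. It uses the existing ethics committee, needs no new board, and changes neither the sample size, the outcomes nor the analysis. The article describes a trial still recruiting, with closure planned for December 2024, so on that timetable the change could still benefit participants.

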### Sample size consideration

According to the result of the pilot study, the sample size will be 200 (100 in the APP group and 100 in the control group respectively) if taking the incidence of PPCs within the first 30 PODs as the primary outcome and 20%the as loss rate [30].

### Data collection and analysis plan

All data will be collected and stored in case report form by two well-trained assessors (WG, MC) independently. Any discrepancies will be checked by the same two assessors to ensure accuracy and authenticity. All information will be aggregated in the final trial dataset, which will be accessible only to LS and will only be shared with research team members upon request for the completion of the designated learning task. All information related to patient identification will be hidden before being uploaded to a public database. Descriptive analyzes of the patient population will include reporting means (with SDs) for normally distributed variables, medians (with Q1, Q3) for skew-distributed variables, and frequencies (with percentages) for categorical variables. Student t-tests will be conducted to analyze normally distributed variables. The Mann-Whitney *U* test will be used for skew-distributed data and ordered categorical variables. Chi-squared tests will be used to analyze binary or unordered categorical variables. The balance of baseline data and differences in postoperative outcomes will be assessed in terms of the above variables. To control other covariates, including stratification factors (gender and fracture type) and baseline variables that have potential relation with the outcome, as well as any such variable that appears imbalanced between the APP group and control group, multiple logistic regression model will be conducted to analyze the related factors of PPCs at each point of time (POD 30 and 90). Similarly, we will perform a multivariate linear regression analysis to determine which variables are independently related to the difference in PaO_2_ between POD 4 and EV. All analyses will be performed using the SPSS 23.0 software. Any outcome data collected for participants who discontinued or deviated from the intervention protocol will be listed. Primary and secondary outcome analysis will not allow missing data. Other missing values will be assumed to show no significant difference from other data we have collected; If missing values suggest that the missingness is not random, we will assess the potential impact of missing data on our results via a developmental model.

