As reported, the duration of the therapeutic prone position was at least up to 2 h per day was considered to be effective [60]. However, as a preventive measure for PPCs, the suitable duration of APP is still uncertain. According to the previous attempt, the tolerance limitation for one time to keep a prone position in the first 3 consecutive PODs for most patients receiving hip fracture surgery was not longer than 30 min. Furthermore, we have no indication to use sedative drugs for conscious patients in the general ward to prolong the time in a prone position as if in the intensive care unit, which is unethical. According to the preliminary trial results, there were significant differences in some outcomes between the APP group and control group, such as the difference in PaO_2_ between POD 4 and EV, and the incidence of PPCs within the first 30 PODs. If the results of the RCT prove the efficacy of postoperative APP in geriatric patients with hip fractures, this research could share our experience and help develop subsequent implementation procedures.

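### The plan only lists outcome data of patients who stop or deviate and bars missing outcomes despite 20% planned loss, so analysis by assigned arm is not secured and complete-case analysis is the practical result

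*Protocol article*

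**What the plan says.** The Data collection and analysis plan first sets out the tests and regressions. It then gives three rules on deviation and missing data:

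- Deviators: "Any outcome data collected for participants who discontinued or deviated from the intervention protocol will be listed".
- Missing outcomes: "Primary and secondary outcome analysis will not allow missing data".
- Everything else: "Other missing values will be assumed to show no significant difference from other data we have collected", with a developmental model, not described further, if missingness looks non-random.

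The article names no analysis population. Sample size consideration states that "the sample size will be 200 (100 in the APP group and 100 in the control group respectively", and that this holds "if taking the incidence of PPCs within the first 30 PODs as the primary outcome and 20%the as loss rate".

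Intervention applies the prone sessions to the APP arm only. They end on certain adverse events, or if "the patients report that he/she cannot tolerate the prone position, the intervention should be stopped immediately". Prone time and the reasons for termination are recorded, but nothing says that they define who is analysed. For oxygenation, Secondary outcome states: "On the morning of POD 4, the patient will undergo arterial blood gas analysis while inhaling room air".

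**The concern.** The article is not silent here; it gives rules, and they leave the main comparison open. After the tests and models are set out, patients who discontinue or deviate get a different verb. Listing data is not the same as analysing them in the randomised arm. The bar on missing outcomes meets an expected loss of one patient in five, and the only missing-data method is attached to other values. An analyst who followed the text would have to drop patients without a 30-day status.

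Three features of this trial make that matter.

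- **Stopping is one-sided and may be prognostic.** Only APP patients have sessions to stop. The triggers in Intervention include chest tightness and difficulty breathing. Secondary outcome names dyspnoea and chest distress among the symptoms that start a complication work-up. Patients who stop may therefore carry a higher PPC risk.
- **Stopping is foreseeable.** The Discussion reports that single-session tolerance in the first three days "for most patients receiving hip fracture surgery was not longer than 30 min", while Intervention sets half an hour as the minimum session.
- **PaO2 on day 4 can be missing for a reason.** A patient who has died or cannot come off oxygen has no room-air value, and under the second rule leaves both PaO2 analyses.

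At stake is whether the result is a comparison of randomised groups.

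**Working it through.** **1. The plan's own figure.** The total of 200 cannot be rebuilt, because the article gives no alpha, power or pilot PPC rates. Only the loss step can be checked:

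- n/(1 − d) = 80/(1 − 0.20) = 100 per arm
- expected loss = 0.20 × 200 = 40; patients left = 160

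So 200 fits 80 evaluable patients per arm. The base number is not stated, and 83 × 1.20 = 99.6 also rounds to 100. The figure is compatible with a complete-case plan but does not prove one.

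**2. How much the missing outcomes could matter.** The only overall PPC rate in the article is the literature figure of up to 12.6% (Introduction), which is not a stated planning rate. At that rate 160 × 0.126 = 20.2 events, about half the 40 expected losses. As an invented example, take 5/80 on APP against 10/80 on control, with 20 lost per arm:

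- observed difference: 6.25% − 12.5% = −6.25 points
- APP bounds: 5/100 to 25/100; control bounds: 10/100 to 30/100
- difference: from 5% − 30% = −25 points to 25% − 10% = +15 points

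These are worst-case limits. They treat lost patients as having no PPC information at all.

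**3. What leaving deviators out would do.** This is a conditional check, since no sentence says that they are left out. Assume no true effect and PPC risk p in both arms. Let a share e of the APP arm be dropped, with r times the risk of those who stay. Then:

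- risk in the APP patients kept = p / ((1 − e) + e·r)
- spurious difference = p − that risk
- rejection rate: pooled two-proportion z test, two-sided 5% (assumed), 100 controls against 100(1 − e) APP patients

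| p | e | r | Risk in APP patients kept | Spurious difference (points) | Two-sided rejection |
|---|---|---|---|---|---|
| 12.6% | 10–30% | 1 | 12.6% | 0 | 5.0% |
| 12.6% | 10% | 1.5 | 0.126/1.05 = 12.0% | 0.6 | 5.2% |
| 12.6% | 20% | 2 | 0.126/1.20 = 10.5% | 2.1 | 7.0% |
| 20% | 20% | 2 | 0.200/1.20 = 16.7% | 3.3 | 8.6% |
| 30% | 30% | 3 | 0.300/1.60 = 18.75% | 11.25 | 37.8% |

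Over the whole grid (p 12.6% to 30%, e 10% to 30%, r 1 to 3) the spurious difference runs from 0 to about 11 points and the error from 5% to 38%. The article supplies neither e nor r. With everyone kept in the arm assigned and outcomes complete, the expected difference is 0 and the error 5%, with no change in sample size.

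**The case against.** A reader might infer that the primary comparison is an as-adhered analysis that favours APP. The document does not support that, for these reasons:

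- No sentence excludes deviators, moves them to the other arm or analyses them by prone time. Listing may mean only that their outcomes will be collected and reported.
- Stopping prone sessions does not make the 30-day status missing. Follow-up by visit or telephone covers all patients (Intervention), and a PPC counts wherever it is diagnosed (Primary outcome).
- Bias towards APP needs deviators to be both dropped and at higher risk. Loss to follow-up and missing room-air PaO2 can occur in either arm. If APP works, more control patients may lack a room-air value, and dropping them would work against APP.
- Entry requires tolerance of half an hour prone, which limits later intolerance. The Discussion's remark concerns an earlier attempt, and its limit includes exactly 30 minutes. A very large share of deviators is therefore not shown.
- Many lost patients would have partial data. In-hospital complications are recorded, chest radiography is repeated on day 4, and the Discussion places the peak of PPC diagnosis on that day.

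All of this stands, and it limits the point. It can also be said that populations and imputation belong in an analysis plan that is not shown, and that the missing-data sentence is a follow-up target. That answers less. The article does not defer the matter; it states rules, and a later document would have to override them. A follow-up target does not say what to do with the 20% that the sample size already expects to lose.

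**Conclusion.** The point holds as a badly fixed rule, not as proof of a biased analysis. The text does not commit to analysing patients who stop or deviate in their assigned arm. Its bar on missing outcomes, beside up to 40 expected losses in 200, amounts in practice to complete-case analysis with no stated method for the primary outcome.

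If deviators were left out, the probable direction is towards APP, because discontinuation of prone sessions is confined to that arm and its triggers overlap with PPC symptoms. The size is unknown: 0 to about 11 points under assumed risks and deviation rates, and nil if deviators have the same risk as the rest. For loss and missing PaO2 across both arms, no direction can be given.

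**What to change.** Replace the two sentences with text to this effect:

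1. The primary analysis includes every randomised patient in the arm assigned, whatever prone time was achieved. Any adherence-based analysis is supportive only.
2. Day-30 PPC status is taken from all in-hospital and follow-up records. Status still missing is multiply imputed from arm, baseline covariates and day-4 findings, with a tipping-point sensitivity analysis.
3. For day-4 PaO2 and its change from the emergency visit, the number of patients without a room-air value and the reasons are reported by arm, with a sensitivity analysis. Giving such patients the worst rank is one option, not a requirement.

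The cost is wording and some extra programming, with no additional patients or visits. The estimate may turn out less favourable to APP.
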